## **2.4 Interventions**

### **2.4.1 PA Intervention**

The design of the PA intervention involves a pragmatic methodological approach including non-restrictive eligibility for participation, leaving details of the intervention implementation up to the program trainer (individualized PA program) and allowing the intervention sessions to be conducted by individuals from a variety of backgrounds and levels of experience. Participants in the PA group will undergo a 4-week remotely delivered one-on-one individualized PA programme that will involve weekly 1 hour-long sessions with their program trainer. Participants will be matched with a program trainer and work individually with the trainer for the duration of 4 weeks. Program trainers are certified PA trainers with a background in exercise and health psychology, additional training in suicide risk, and graduate-level coursework in exercise psychology and motivational interviewing.

Prior to the beginning of the intervention, participants will participate in a goal-setting session and will be given a personalized introduction to the program. During this session, participants will meet their program trainer virtually and they will discuss their goals, needs, equipment access, and previous PA experience with the program trainer. After this meeting, the program trainer will develop an individualized and tailored PA program for the participant.

During the intervention period, participants will meet with the program trainer once a week virtually over Zoom for 4 weeks. During these weekly Zoom sessions, participants will engage in 30 minutes of behavioral change coaching with the program trainer using a version of the MoveU.HappyU Workbook that has been adapted for TRD. This behavioral change coaching will involve participants setting weekly goals, assessing goal progression, developing action plans, exploring barriers and enablers to goals, and setting cues or prompts for self-directed PA. After the first 30 minutes, participants will engage in 30 minutes of a structured PA program that is tailored to each participant's needs and goals. The intensity of the PA sessions will be self-selected.

Prior to the start of each PA session, program trainers will ask participants how many minutes of PA they engaged in during the week (excluding the supervised session) as well as the type of activities they engaged in (prompts to include *with who, what, and where [e.g., indoors vs. outdoors]*). This information will be recorded in Research Electronic Data Capture (REDCap) and cross-referenced with the data collected by the Oura App.

Although the PA programme will differ from participant to participant, the overall organization of the weekly PA sessions will be standardized across participants. Specifically, the PA sessions will involve a warmup consisting of 5-7 minutes of light to moderate intensity cardiorespiratory and endurance activities, a conditioning component consisting of 20 minutes of individualized aerobic or resistance exercises and a 3-5 minute cool down/stretch. PA sessions will target major muscle groups such as the chest, shoulders, upper and lower back, abdomen, hips and legs) with a specific emphasis on proper form and technique (e.g., deliberate movements in a controlled manner, moving through the full range of motion of the joint, and utilizing proper breathing techniques). Since the PA program will involve a combination of aerobic and resistance exercises, program trainers will record the proportion/percentage of each type of exercise during the session on REDCap. The Rate of Perceived Exertion (RPE) using the Borg Rating of Perceived Exertion Category-Ratio Scale (BORG-CR-10) scale will be recorded at the end of each supervised session by the program trainer to measure perceived effort and affective valence (i.e., pleasure/displeasure of exercise). Additionally, the Talk Test will be used to encourage engagement in moderate-to-vigorous intensity PA. In addition, participants will complete the Feelings Scale and the Felt Arousal Scale and responses will be recorded by the program trainer on REDCap.

After each session, participants are also asked to complete homework and rate how satisfied they were with the delivery of the session using the adapted MoveU.HappyU Workbook. Their satisfaction rating will be recorded on REDCap by the program trainer. Participants will be

instructed to engage in PA for 150 minutes in total, at 50-65% of their maximum work capacity, each week. This can be done by practicing PA between 3-5 times per week. It is important to note that participants are only engaging in PA with the program trainer once per week for 30 minutes. The remaining 120 minutes of PA will be completed independently by the participant, on their own time, according to the tailored PA program developed by their program trainer. Upon completion of the program, participants will complete an exit survey to evaluate their experiences of the program. Additionally, they will meet with a member of the study staff for a semi-structured interview to further discuss the acceptability of the PA program.

#### 2.4.2 Wearable Device (Oura Ring)

In this study, we will use a digital wearable device to continuously collect longitudinal, passive data that will help us monitor activity, sleep, and physiological data related to stress and mental health symptoms. For this, we will use the commercially available wearable device, Oura Ring, which collects sleep and activity data, as well as a series of physiological signals that may be potentially relevant in the context of PA and mental health. This device is identified as a passive wearable device that can be used without obstructing one's daily life. Detailed information on the sensors and vital signs collected by Oura Ring are summarized in Table 1.

**Table 1.** Description of the wearable device to be used and vital signs to be collected

| Description                                                                                                                                                                                                                                                                                                                                                                                         | Data Transfer                                                                                                                                                                                                                                                                                                                                                                                      | Data elements                                                                                                                                                                                                                                                                                            |
|-----------------------------------------------------------------------------------------------------------------------------------------------------------------------------------------------------------------------------------------------------------------------------------------------------------------------------------------------------------------------------------------------------|----------------------------------------------------------------------------------------------------------------------------------------------------------------------------------------------------------------------------------------------------------------------------------------------------------------------------------------------------------------------------------------------------|----------------------------------------------------------------------------------------------------------------------------------------------------------------------------------------------------------------------------------------------------------------------------------------------------------|
| The Oura Ring  is a smart ring that is worn on the finger and collects heart rate and respiration rate from an individual. It uses advanced sensor technology to allow for precise, personalized health insights about one's body. This device measures daily activity, oxygen saturation, heart rate, heart rate variability, and body temperature variation. Additionally, the device | Participants will download and log on to the Oura Ring  mobile app using the study email credentials. The Oura Ring  connects to a user's smartphone via Bluetooth. It will collect data locally and send it to the mobile app when synced. Once the Oura Ring  app has internet access, its data will be transferred to and stored on its respective servers. | 
 
● Heart rate
 
● Respiratory rate
 
● Daily activity
 
● Heart rate variability
 
● Oxygen saturation
 
● Body temperature variation (delta)
 
● Individual's readiness
 
● Sleep
 
● Activity
 
 |

|                                                        |  |  |
|--------------------------------------------------------|--|--|
| scores an individual's readiness, sleep, and activity. |  |  |
|--------------------------------------------------------|--|--|

Upon acceptance to the study, the Oura Ring wearable device will be made available with its respective Privacy Policy for participants to read. Passive data collection on the wearable device will begin approximately 3 weeks before the interventional period begins (to establish baseline parameters). The procedure for the use of the wearable device is as follows:

- (1) Participants will be offered to consent to collecting data from the Oura Ring wearable device.
- (2) Members of the research team will create secure and unique IDs, dummy emails, and passwords to be given to each participant for de-identification.
- (3) Participants will collect the Oura Ring wearable device (during the baseline visit), download its respective mobile app on their personal device, and log in using the given email and password.
- (4) The duration of participants using the digital platform will comprise approximately 13 weeks.
- (5) Once participants have completed the study, the devices and accounts will be returned, cleaned, and formatted. Participant data will only be accessible by the research team and the participant using it.
  - (a) Participants will return the ring and charger to the IPP at St. Michael's Hospital, Unity Health Toronto (SMH-UHT) during their final assessment visit.

The participant will pick up the Oura Ring wearable device at the IPP at SMH-UHT during their scheduled baseline visit. At that time, the study team will assist the participant with selecting the appropriate ring size (using a sizing kit) and setting up their account on the Oura mobile application. Participants will have access to the study coordinator's contact information in case any technical problems and/or questions arise.

The wearable device will be evaluated for its feasibility to collect physiological data in naturalistic settings (i.e., dropout rates, amount of data collected, missing data). It will be helpful in tracking individual trends over time, which will potentially provide us with a better understanding of physiological responses related to PA and depression. These multivariate models will help us build prediction tools, which could be an important factor in the design of decision support tools related

to mental health. We will incorporate sex/gender- and age-based analysis throughout the study to adjust the models as needed.

The description of the physiological signals to be collected by the Oura Ring is provided below:

1. Sleep information: The Oura Ring performs sleep analysis and stores a set of measurement parameters that summarize each period. The ring calculates the sleep period specific parameters within four hours from the period end, but sleep analysis is always triggered when participants open the application. These parameters include sleep related data such as bedtime, total duration, awake, light, rapid eye movement, and deep sleep durations. It also collects physiological signals such as heart rate, respiratory rate, heart rate variability, and body temperature changes.
2. Activity information: Activity summary contains daily activity summary values and detailed activity levels. Activity levels are expressed in metabolic equivalent of task minutes (metabolic equivalent minutes). The Oura Ring tracks activity based on movement and presents the activity score based on the duration of low, medium, and high activity levels. The movement is also used for a daily step count and an estimation of calories.
3. Readiness information: Readiness score is interpreted from sleep, activity, resting heart rate, heart rate variability, recovery index, and body temperature scores. A readiness score above 85% indicates that the wearer is well recovered. A score below 70% usually means that an essential readiness contributor, such as body temperature or previous night's sleep, falls outside a wearer's normal range, or clearly differs from recommended, science-based values.

### 2.4.3 REDCap

REDCap (<https://www.project-redcap.org>) software supported by the Applied Health Research Centre at Unity Health Toronto (UHT) will be used for data collection and overall study data management over the course of this project. REDCap is an open-source, web-based clinical data management and electronic data capture system and database. The system is developed and managed in compliance with UHT privacy, the Health Insurance Portability and Accountability Act, the Personal Information Protection and Electronic Documents Act, and Food and Drug Administration 21 Code of Federal Regulations Part 11 regulations, providing functions such as defined user roles and privileges, user authentication and encryption for in-transit data, de-identification of protected health information and comprehensive auditing features to record and monitor access and changes to data. This system will be used to send scheduled questionnaires to participants and store active data and data monitoring and for the query and export of datasets for statistical analysis and modeling.

Access to REDCap will be secured through a secure web portal and protected by multiple levels of authentication. A Project Coordinator will be assigned the project administrative privileges for study configuration, data collection management, and quality control.

Upon acceptance to the study, participants will complete mental health questionnaires on a daily and weekly basis. To complete these questionnaires, participants will receive an email notification with the REDCap survey link to their personal email address. Upon receiving the link, participants will answer the self-report questionnaires provided through the link. Active data will be sent to and stored on the REDCap server and will be linked by the unique ID for final analysis. Access to this data will only be granted to the project administrator to download the data from the REDCap server for analysis.

#### **2.4.4 Concomitant medication**

Before the intervention, research staff will document all medications taken by participants on a regular basis. No changes to treatment are allowed one month (28 days) before screening due to the probable impact on psychiatric symptoms. Participation in the study will not alter the standard of care, including any required changes to treatment regimens. While the study aims to avoid any changes to participants' treatment during the 4-week randomized intervention phase and the 6-week follow-up phase, changes that are required clinically to manage an acute clinical deterioration or adverse effects will be allowed and recorded; according to the treat (ITT) principle, participants whose treatment is changed will remain in the trial.

#### **2.4.5 Concomitant care**

Before the intervention, research staff will confirm that participants have not recently initiated treatment with psychotherapy, brain stimulation, or ketamine. Following the ITT principle, if any changes to treatment are required, the participant will remain in the trial.

#### **2.4.6 Compliance**

Similar studies among clinical TRD samples have shown promising compliance rates of 91% and 94%. Even though the weekly PA sessions via Zoom will be supervised, the other sessions will be unsupervised. As such, treatment adherence will not be known with 100% accuracy but can be estimated using self-report validated by Oura Ring data. Nevertheless, prior studies have shown that exercise interventions in which participants are able to self-select exercise intensity promote treatment adherence. The introduction of exercise regimes that increase in intensity incrementally and give the participants control over the level of intensity tend to increase participants' enjoyment of the exercise and thus increase compliance rates. Participant compliance will be assessed on a weekly basis during the PA sessions with the program trainer using the adapted MoveU.HappyU Workbook wherein participants will be asked to rate their progress towards their PA goal from the previous week. In addition, program trainers will ask participants the number of minutes they spent engaging in PA during the week (excluding the

supervised session) and the kinds of activities they engaged in. Additionally, to ensure that participants are completing the scales and using the Oura Ring as required, weekly compliance calls will be made to participants who are missing Oura data for 3 or more days in the past week or if REDCap data is missing.

## **2.5 Outcomes**

All outcomes will be assessed at different stages of the study. Please refer to the study's timeline, Section 2.6.1, for a detailed depiction of the nature and frequency of all assessments. All study personnel administered scales will occur via phone call, Zoom or in-person by trained blinded (as applicable) study staff members. Self-report questionnaires will be completed via REDCap.

### **2.5.1 Primary outcome measures**

To evaluate the feasibility of randomizing adult participants with TRD to a PA programme add-on to TAU or TAU, primary outcomes will include recruitment rate (minimum threshold: 2 participants/month), withdrawal rate (maximum threshold: 20%), data completion rate (minimum threshold: 80%) and adherence rate (minimum threshold: 80%). Qualitative data from the exit survey and semi-structured interview will be used to evaluate the acceptability of the PA intervention. A full trial will be considered feasible with this design if the upper 95% confidence limit for withdrawal rate is  $\leq 20\%$  and both of the lower 95% confidence limits for data completion rate and adherence rate are  $\geq 80\%$ . If feasibility thresholds are not met, our team will evaluate the reasons and determine whether they could be addressed with protocol modifications. Data on the primary endpoints will be collected and recorded throughout the study. Tabulation and analysis will occur after all study-related data have been collected and follow-up of all study subjects is complete.

In addition to the exit survey, semi-structured qualitative interviews will be conducted with the participants to determine the acceptability of the PA intervention. Interviews will be conducted one-on-one with a designated member of the study staff. Interviews will be recorded (with the participants' permission), transcribed verbatim, and analyzed using reflexive thematic analysis to explore the participant's experiences in the PA program. The audio of the interview will be recorded using Zoom and will be stored on an encrypted, password-protected hard drive.

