### Primary Aims:

**Aim 1:** To assess the feasibility (recruitment rate, withdrawal rate, adherence rate, and data completion rate) of randomizing adult participants with TRD to a PA programme add-on to TAU or TAU and to assess acceptability (responses on the exit survey and semi-structured qualitative interviews) of the PA programme.

**H1a (Recruitment rate):** Over 15 months, we will be able to recruit and assess 2 participants per month.

**H1b (Withdrawal rate):** The overall withdrawal rates will be no more than 20%.

**H1c (Data completion rate):** The data completion rates will be more than 80% in both treatment arms.

**H1d (Adherence rate):** Adherence rates, including treatment compliance and study completion, will be more than 80% in both treatment arms.

**H1e (Acceptability):** Participants will report satisfaction with the content and delivery of the intervention, as measured by the exit survey and semi-structured qualitative interview.

If feasibility thresholds are not met, our team will evaluate the reasons and determine whether they could be addressed with protocol modifications.

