## **2. METHODS**

### **2.1 Trial Design**

We propose an interventional, randomized, 4-week pilot clinical trial. The trial will enroll 30 participants to generate data for feasibility and acceptability, and to estimate variability of the efficacy outcomes to use in the sample size calculation for future larger scale trials. We will evaluate the feasibility and acceptability of a 4-week remote one-on-one individualized PA programme for participants with TRD (i.e.,  $\geq 2$  failed trials of antidepressant treatment) and in a mild-to-severe major depressive episode (MDE) as measured by a Montgomery-Åsberg Depression Rating Scale (MADRS) total score of  $\geq 7$ , while simultaneously using a digital wearable device (Oura Ring) to monitor participant's physiological data.

Participants will be randomized to one of two treatment arms:

- 1) PA group: Participants in this group will continue TAU and will participate in a 4-week remotely delivered one-on-one individualized PA programme.
- OR
- 2) TAU group: Participants in this group will continue to receive TAU, but will not receive the PA programme add-on. Instead, these participants will be given a handout with the Canadian 24-hour movement guidelines and be told that they are encouraged to engage in PA.

Participants in both groups will use a wearable device, known as an Oura Ring, to collect passive data related to physiological variables (e.g., sleep, heart rate, activity). Please see Section 2.4.2 for more information on the Oura Ring and Section 2.4.1 for a thorough description of the remotely delivered PA programme. **Figure 1** summarizes the proposed study design. Participants in both treatment arms will continue to receive treatment congruent with Canadian Network for Mood and Anxiety Treatments (CANMAT) guidelines with no changes to treatments 28 days before screening. The study team will also try to keep treatments unchanged during the 4-week randomized intervention phase and the 6-week follow-up phase (Sections 2.4.4 and 2.4.5).

At the end of their participation in the study, participants who were randomized to the TAU group will have access to at least one session with a PA trainer.

[figure not shown]

**Figure 1.** Proposed study design. TAU = treatment as usual, PA = physical activity.

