## 2.7 Sample Size

Because the anticipated effect size is unknown, a formal sample size calculation cannot be completed. For this interventional pilot trial, it is anticipated that 30 participants will be recruited.

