## 2.10 Allocation

If potential participants meet the eligibility criteria, they will be enrolled in the trial and will be randomized in a 2:1 allocation to receive a PA program add-on (experimental group) or TAU (control group). Thus, 20 participants will be randomized to the PA group and 10 participants will be randomized to the TAU group. Block randomization will be computer-generated, and the sample will be stratified for sex given the potential for differences in response in these groups. The randomization schedule will employ random permuted blocks of varying sizes. It will be administered by a member of the study staff.

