## **2.13 Data Analysis**

We are primarily interested in generating essential data on potential feasibility and acceptability issues pertaining to a trial of a remotely-delivered, one-on-one, individualized PA programme vs. TAU in participants with TRD. We will assess feasibility and acceptability using descriptive statistics with counts and proportions for categorical data and means and standard deviations or median and interquartile range, as appropriate, for continuous data. The proportion lost to follow-up will be estimated along with a 95% confidence interval. The upper 95% confidence limit should not exceed 20% to proceed. The proportion compliant with the protocol, including treatment compliance as well as study completion and complete data on clinical outcomes (i.e., the per-protocol group) will be estimated with a 95% confidence interval. For validity, this should be fairly high so that the lower 95% confidence limit is  $> 80\%$ . See Section 2.13.2 for additional acceptability analyses. We will estimate the means, standard deviations, and the correlations of HAM-D-17 and its changes over the study duration and over the follow-up. Also, we will estimate means, standard deviations and pre-post correlations of GAD-2, PHQ-2, GAD-7, WHO-5, and PHQ-9. Initial analyses will summarize socio-demographic and clinical characteristics by treatment group. Comparative analyses will not be performed on clinical outcomes. Instead, means, standard deviations, and pre-post correlations will be estimated for continuous outcomes while proportions will be estimated for binary outcomes. One of the purposes of the vanguard phase is to measure outcomes for use on refining final sample size estimates but retain the ability to use the data collected in the final trial.

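### The protocol sets two different feasibility criteria at the same 20% and 80% cut-offs, one on observed rates and one on 95% confidence limits, and leaves recruitment out of the feasibility sentence

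*Protocol*

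**What the plan says.** Section 1.2 (Primary Aims) words the hypotheses as rates. H1b reads "The overall withdrawal rates will be no more than 20" per cent. H1c reads "The data completion rates will be more than 80% in both treatment arms", and H1d sets the same 80% in both arms for adherence, which it defines to include treatment compliance and study completion. H1a expects 2 participants per month over 15 months.

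Section 2.5.1 lists four thresholds: recruitment 2 per month, withdrawal 20%, data completion 80% and adherence 80%. The decision sentence follows: "A full trial will be considered feasible with this design if the upper 95% confidence limit for withdrawal rate is" at or below 20% and the lower 95% limits for completion and adherence are both at or above 80%. It mentions neither recruitment nor arms.

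Section 2.13 applies a limit rule to the proportion lost to follow-up: "The upper 95% confidence limit should not exceed 20% to proceed". It then asks for a lower 95% limit above 80% on a single per-protocol proportion that combines compliance, study completion and complete clinical data.

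On size, section 2.1 says "The trial will enroll 30 participants to generate data for feasibility and acceptability", and section 2.10 says "Thus, 20 participants will be randomized to the PA group and 10 participants will be randomized to the TAU group". Sections 1.2 and 2.5.1 both say that if thresholds are missed, the team will look at the reasons and at possible protocol changes.

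**The concern.** A hypothesis that a rate is at most 20%, judged on the observed rate, and a rule that the upper confidence limit is at most 20% are different criteria. At N=30 they lie far apart. Feasibility is the primary aim and this is the protocol's only quantitative decision rule, so the reported conclusion would depend on which section is followed.

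Two further mismatches make the rule hard to apply. Section 2.5.1 judges withdrawal, completion and adherence separately, while section 2.13 judges loss to follow-up and one composite. Recruitment has a threshold but no place in the sentence that declares a full trial feasible, so on that sentence alone a trial that recruited too slowly could still be called feasible.

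**Working it through.** **Inputs.** N=30 (section 2.1; also 2 per month × 15 months = 30, section 2.8). Arms of 20 and 10 (section 2.10). Cut-offs of 20% and 80% (sections 1.2, 2.5.1, 2.13). The protocol names no interval method. Assumption: two-sided 95% Clopper-Pearson (exact), with alternatives shown below.

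**What the rates in H1 allow.** 0.20 × 30 = 6, so up to 6 withdrawals meet H1b. Above 80% means more than 0.80 × 30 = 24, so at least 25/30. In the PA arm it means more than 0.80 × 20 = 16, so at least 17/20.

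**What the limit rule allows, pooled.** For x failures in n, the exact upper limit is the 97.5th percentile of a Beta(x+1, n−x) distribution. The lower limit for n−x successes is one minus that.

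| Failures of 30 | Upper limit, failures | Lower limit, successes | Rule |
|---|---|---|---|
| 0 | 11.6% | 88.4% | pass |
| 1 | 17.2% | 82.8% (29/30) | pass |
| 2 | 22.1% | 77.9% (28/30) | fail |
| 6 | 38.6% | 61.4% (24/30) | fail |

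So the rule means at most 1/30 withdrawals and at least 29/30 complete and adherent.

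**Sensitivity to the interval at 2/30.** Two-sided upper limits are 21.3% (Wilson), 22.4% (Agresti-Coull) and 20.3% (mid-P), which fail, and 19.7% (Jeffreys) and 15.6% (Wald), which pass. A one-sided exact limit is 19.5% and passes. None of these two-sided methods passes 3/30 (Wald 20.7%, Jeffreys 24.3%). Of the one-sided variants run, only Wald passes 3/30 (19.0%). No method comes near the 6 that H1b tolerates.

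**Where the two criteria disagree.** Under exact limits, 2 to 6 withdrawals (6.7% to 20%) meet H1b and fail the rule. If the interval allows 2, the range is 3 to 6.

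**Chance of passing one criterion.** With true failure probability p and at most 1 failure allowed, P = (1−p)^30 + 30p(1−p)^29.
- p = 2%: 0.88.
- p = 5%: 0.215 + 0.339 = 0.55.
- p = 10%: 0.042 + 0.141 = 0.18.
- p = 20%: 0.01.

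If 2 failures are allowed, the figures at 5% and 10% are 0.81 and 0.41. Under H1b's own count (at most 6), the figure at 10% is 0.97.

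**If the limit rule were applied within arms.** With no failures, the exact lower limit is 0.025^(1/n). For n=20 this is 83.2%, so 20/20 passes; 19/20 gives 75.1% and fails. For n=10 it is 69.2%, so even 10/10 fails. Two-sided Wilson (72.2%), mid-P (74.1%) and Jeffreys (78.3%) agree for 10/10. Among two-sided methods only the Wald interval, which has zero width at 10/10, passes.

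**The case against.** A confidence-limit criterion is a legitimate, conservative way to test a claim that a rate is at most 20%. It appears in both 2.5.1 and 2.13, so it looks deliberate. This stands: the sponsor may keep it. It does not remove the conflict, because H1b to H1d and the listed thresholds are worded as rates, and nothing tells a reader that 20% in effect means 1 in 30.

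The interval method is normally left to the statistical analysis plan. That is fair, and its absence alone is no finding. But choosing a method moves the limit only from 1 to 2 failures (3 at the most lenient one-sided choice), so it cannot reconcile the rule with 6.

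A reader might infer that the limit rule cannot work at this size. The documents do not support that: pooled, it passes with 0 or 1 failures, which is likely if true failure rates are near 2%. A reader might also infer that the TAU arm makes the rule unattainable. Sections 2.5.1 and 2.13 state the limit rule without arms, and the both-arms wording of H1c and H1d carries no confidence limit, so this follows only if the two are joined.

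It is also tempting to feed the compliance figures of 91% and 94% in section 2.4.6 into the binomial. The protocol does not say whether these are shares of participants or of sessions attended, so they cannot carry that weight.

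Finally, missing a threshold triggers a review and possible modification, not a stop, and since recruitment is a listed threshold a shortfall would presumably be reviewed too. This limits the damage but still leaves the feasibility verdict undefined.

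**Conclusion.** The point holds. The protocol contains two criteria at the same cut-offs that give opposite conclusions for 2 to 6 withdrawals out of 30 under two-sided exact limits (3 to 6 under Jeffreys, Wald or one-sided exact limits). Read as written and pooled, the limit rule is strict rather than impossible: each criterion passes 55% of the time at a true failure rate of 5%, and 18% at 10%. Within-arm use would require 20/20 in PA and could not be met in TAU under exact limits, but that depends on a per-arm reading which the decision sentence does not state. Recruitment is missing from the feasibility sentence, and 2.5.1 and 2.13 judge different quantities.

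These results assume all 30 participants in the denominator and independent outcomes between participants. The reading of H1b as up to 6/30 takes the hypothesis as a statement about the observed rate. No joint probability for the three criteria is offered, because it would rest on inputs that the protocol does not give.

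**What to change.** State one rule, in the same words, in sections 1.2, 2.5.1 and 2.13. Apply it to the same quantities (choose withdrawal or loss to follow-up; separate rates or the composite), with its counts at N=30 and the interval method. Two options:

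- **(a) Decide on the observed rates in H1.** Withdrawals at most 6/30, complete data at least 25/30, adherence at least 17/20 in the PA arm. Report exact 95% intervals beside them as precision. The cost is less assurance: at a true withdrawal rate of 25%, this passes 35% of the time.
- **(b) Keep the confidence-limit rule.** Say that it is pooled over 30 and that, with two-sided exact limits, it means at most 1/30 withdrawals and at least 29/30 complete and adherent. Reword H1b to H1d to match. The cost is the low chance of passing shown above, even when true failure rates are 5% to 10%.

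Under either option, add recruitment of at least 2 per month to the feasibility sentence, and do not apply confidence limits within the TAU arm. Keep the existing sentence on reviewing missed thresholds. The change is wording only, needs no extra participants, and should be made before the feasibility data are tabulated.
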